## Abstract

**Introduction:**

Adequately addressing the needs of patients at the end of life and their relatives is pivotal in preventing unnecessary suffering and optimising their quality of life. The purpose of the iLIVE study is to contribute to high-quality personalised care at the end of life in different countries and cultures, by investigating the experiences, concerns, preferences and use of care of terminally ill patients and their families.

**Methods and analysis:**

The iLIVE study is an international cohort study in which patients with an estimated life expectancy of 6 months or less are followed up until they die. In total, 2200 patients will be included in 11 countries, that is, 200 per country. In addition, one relative per patient is invited to participate. All participants will be asked to fill in a questionnaire, at baseline and after 4 weeks. If a patient dies within 6 months of follow-up, the relative will be asked to fill in a post-bereavement questionnaire. Healthcare use in the last week of life will be evaluated as well; healthcare staff who attended the patient will be asked to fill in a brief questionnaire to evaluate the care that was provided. Qualitative interviews will be conducted with patients, relatives and healthcare professionals in all countries to gain more in-depth insights.

**Ethics and dissemination:**

The cohort study has been approved by ethics committees and the institutional review boards (IRBs) of participating institutes in all countries. Results will be disseminated through the project website, publications in scientific journals and at conferences. Within the project, there will be a working group focusing on enhancing the engagement of the community at large with the reality of death and dying.

**Trial registration number:**

NCT04271085.

Strengths and limitations of this studyDue to the international nature of this study, we are able to investigate end-of-life experiences across different cultures and among groups varying by age, gender, illness and care setting.This study combines the perspectives of the most relevant stakeholders: patients who are in the last phase of life and their relatives, as well as healthcare staff providing end-of-life care.The study population is relatively large which enables to perform subgroup analyses.Although patients in the last phase of life and their caregivers have repeatedly reported to appreciate being given the opportunity to participate in research studies, completing a questionnaire about concerns, preferences and expectations concerning the end of life can be uncomfortable.

## Introduction

Over the past decades, increasing attention has been given to improving care for people in the last phase of life. Literature suggests that most people wish to be free from pain and other symptoms, to be treated with dignity and respect, and to maintain a sense of autonomy and control over their last days.^1–4^ In addition, many individuals wish to be informed of their limited life expectancy.^5^ However, there is a substantial amount of variation in the definition of a ‘good death’. Preferences for the end of life are dynamic and influenced by individual and multidimensional characteristics, such as age, gender, illness, care setting, financial resources, culture and social relationships.^6^

Medical care at the end of life is not optimally addressing the needs and preferences of all patients.^7^ This is in many cases caused by barriers such as the unpredictable course of a terminal illness, communication difficulties and the complexity of care needs of dying patients and their families.^8^ Many terminally ill patients are, for instance, unable to express their goals and preferences for medical treatment or care, due to physical deterioration or mental incapacity.^9 10^ Moreover, since clinicians tend to focus on diagnosis, therapy and cure, the imminence of death is often not openly and timely acknowledged in patients with an advancing chronic illness.^11 12^ A recent longitudinal study reported that end-of-life care was discussed between physicians and patients with terminal cancer in less than 20% of cases, and the frequency of these discussions only increased significantly in the last month of life.^13^ Consequently, patients often receive treatment aimed at prolonging life until a very late stage in their illness trajectory, with a considerable burden for the patient.^14^ Inadequately addressing the needs of the patients not only deteriorates the quality of patients’ last phase of life^15^ but also increases the risk of complicated grief in bereaved family members.^16^

So far, studies have mostly explored the perspectives and experiences regarding factors that are important in end-of-life care of citizens and physicians,^17–19^ but the need to include the perspective of patients and their relatives has been acknowledged as well.^4 8 20^ Studies investigating the needs and preferences of patients in their last phase of life have mostly included patients with cancer, and studied preferences on specific components of palliative care.^21^ Little is known on patients’ concerns, goals and sources of strength during their last phase of life.^22^ In addition, no studies have investigated these aspects within a context of diversity in diagnosis, culture, gender and age.

We expect that patients in the last phase of life consider dignity, respect, social relations, autonomy, symptoms and pain control as important. Although some of these themes may be universal, we hypothesise that differences will exist in concerns, expectations and preferences based on gender, age, illness, care setting and culture.

The first aim of the iLIVE study is to provide in-depth understanding of the experiences, concerns, expectations and preferences of patients in the last phase of life and their relatives. The second aim is to assess variability in these concerns, expectations and preferences by culture, gender, and age, healthcare-related and socioeconomic factors. The international character of the iLIVE study provides a framework for unprecedented international comparative insights. A better understanding of needs and outcomes in end-of-life care will thus contribute to the development and advancement of policies to support dignified dying in various cultures and settings.

## Methods and analysis

### Study design and setting

The iLIVE study is a prospective observational cohort study involving terminally ill patients in hospital and non-hospital sites in 11 participating countries: Argentina, Germany, Iceland, the Netherlands, New Zealand, Norway, Slovenia, Sweden, Switzerland, Spain and the United Kingdom (UK). Countries from three continents over the world were included in the study to ensure cultural diversity within the study population. Terminally ill patients will be followed until they die or for a maximum of 6 months after inclusion. Participating patients and one of their relatives will complete questionnaires about their experiences, concerns, expectations and preferences around dying and use of end-of-life care. This 4-year study started in September 2020 and is currently ongoing.

In order to have a diverse study population regarding clinical and sociodemographic characteristics, we will recruit participants from different types of clinical settings. Patients will be recruited in the 11 participating countries, from a total of 20 hospitals (oncology, internal medicine, surgery, palliative care unit, medical physics, thoracic medicine and pulmonology departments), 7 specialised palliative care institutes and 8 out-of-hospital settings (nursing homes).

### Study population

In total, 2200 patients with a maximum estimated life expectancy of 6 months will be included, regardless of their diagnosis, gender or place of residence (table 1). Eligibility is assessed using a modified version of the Gold Standards Framework Proactive Identification Guidance (GSF-PIG) and the Supportive and Palliative Care Indicators Tool 2017 (SPICT).^20^ The GSF-PIG starts with the ‘surprise question’, asking whether the physician would be surprised if a patient were to die within 1 year.^23^ For the present study, we adapted this question into whether the physician would be surprised if a patient were to die within 6 months. If the physician is uncertain about the surprise question, the patient is eligible when at least one SPICT indicator is present.^24^ SPICT is a tool to identify persons with poor or deteriorating health for assessment and care planning, using general indicators and clinical signs of life-limiting conditions (online supplemental table 1). All physicians will be informed on how to apply the GSF-PIG and the SPICT tool to assess eligibility.

10.1136/bmjopen-2021-057229.supp1Supplementary data

**Table 1 T1:** Inclusion and exclusion criteria for patients and relatives

Inclusion criteria for patients	Exclusion criteria for patients and relatives
18 years of age or older	Unable to provide informed consent
Attending physician would not be surprised if the patient were to die within 6 months	Incapable of filling in questionnaires in the country’s main language or in English
In case of uncertainty about surprise question: at least one SPICT indicator	
Awareness that recovery is unlikely	
Written informed consent to participate	
**Inclusion criteria for relatives**	
18 years of age or older	
Awareness that recovery of the patient is unlikely	
Written informed consent to participate	

SPICT, Supportive and Palliative Care Indicators Tool 2017.

Participating patients are asked to identify a relative, for instance, a family member or friend. Relatives are eligible if they are 18 years of age or older. Patients and relatives need to be aware that the patient is unlikely to recover from his or her illness. The exclusion criteria for patients also apply to relatives.

### Recruitment procedure

In the 11 countries, across all participating clinical sites, physicians are responsible for screening patients for eligibility. All consecutive patients admitted to a clinical ward or visiting an outpatient clinic will be screened for eligibility. Eligible patients are informed about the study by their attending physician or nurse, who provides them with an information leaflet. If patients agree to be informed about study participation, a researcher or research nurse from the local study team contacts them, answers their questions and asks them if they consent to participate. If the patient consents, the researcher asks them to consider whether a close relative might also be willing to participate. After obtaining written informed consent from patients and, if applicable, relatives, they will be asked to fill in the baseline questionnaire.

In each country, five patients, five relatives and five healthcare professionals will be interviewed. Patients and relatives completing the questionnaire face-to-face will be asked whether they are interested in an additional in-depth interview. Patients and relatives completing the questionnaire online or on paper (by post) will be approached by telephone. Patients and relatives who do not participate in the questionnaire study are also allowed to participate. If patients and/or relatives are eligible and interested, the researcher or research nurse approaches them to explain further procedures and to conduct the interview. They will have the option of participating in a face-to-face or Skype interview.

Interviews will be conducted with healthcare professionals who are employed in the participating sites. Two criteria will be guiding the selection of healthcare professionals: (1) their work includes end-of-life care and (2) they have several years of experience with end-of-life care. There will be variation in profession and work setting among participants. The healthcare professional will be contacted by telephone or email inviting them to take part in the study.

### Measurements

The iLIVE cohort study includes several measurements (table 2):

Questionnaires. Patients, relatives and attending physicians are asked to fill in questionnaires. Patients and relatives will complete questionnaires on enrolment in the study (baseline assessment) and 4 weeks later (follow-up 1). For patients who die during the follow-up period of 6 months, relatives will also complete a questionnaire 8–10 weeks after the death of the patient (follow-up 2). Questionnaires for patients and relatives are administered on paper, online or through telephone or face-to-face interviews. Physicians will complete a paper questionnaire at patient enrolment (baseline assessment) and after the death of a patient (follow-up 2).

**Table 2 T2:** Measurements among patients, relatives and physicians within the iLIVE project

I. Measured by questionnaire	Measurement instrument
Patients	
Concerns, expectations and preferences of patients around dying and end-of-life care	Self-developed questions adapted from the Serious Illness Conversation Guide^44^ and the AEOLI questionnaire^45^
Symptom load	Edmonton Symptom Assessment System (ESAS)^46^
Health-related quality of life (HRQoL) and well-being	EORTC QLQ-C15-PAL quality of life question^47^ and EuroQol 5 Dimension questionnaire (EQ-5D-5L)^48^ ICECAP Supportive Care Measure (ICECAP-SCM)^49^
Attitudes towards euthanasia*	10-item Euthanasia scale^50^
Health and social care resource use, absenteeism from work	(Partial) Health Economics Questionnaire (HEQ)^51^
Sociodemographic characteristics	Self-developed questions and HEQ
Relatives	
Concerns, expectations and preferences around dying and end-of-life care	Self-developed questions inspired by the Serious Illness Conversation Guide and the AEOLI questionnaire
Health-related quality of life (HRQoL)	EORTC QLQ-C15-PAL and EQ-5D-5L
Well-being	ICECAP Close Person Questionnaire (ICECAP-CPM)^52^
Informal care provision	iMTA Valuation of Informal Care Questionnaire (iVICQ)^53^ and Informal Care Cost Assessment Questionnaire (CIIQ)^54^
Attitudes towards euthanasia	10-item Euthanasia scale
Bereavement	Hogan Grief Reaction Checklist (HGRC, despair and personal growth subscales)^55^
Quality of care for dying patients	International questionnaire Care of the Dying Evaluation (iCODE)^56^
Physicians	
Patients’ diagnosis, co-morbidities and life expectancy, perspective on patients’ treatment aims and functional status	Based on the SPICT-criteria and the Australian version of the Karnofsky Performance Status^57^
Evaluation of care in the dying phase	Adapted and based on the Swedish Quality of Dying Registry^58^
**II. Obtained from medical files**	
Use of medical interventions, medication and costs of medical care in the last week of life	
Patient survival	
**III. Obtained from qualitative interviews**	
In-depth insights into experiences, concerns, expectations and preferences around dying and end-of-life care among patients, relatives and healthcare professionals	

*In Norway and Iceland, one self-developed question will be used instead of the 10-item Euthanasia scale. No questions will be asked about euthanasia in Germany. Researchers from these countries were concerned that study participants would become anxious by these questions.

Completing the questionnaire will take approximately 30–45 min. In the online version of the questionnaire, participants are allowed to save their answers and continue at a later time point. The same is applicable to completing the paper version of the questionnaire and the face-to-face interview.

#### Baseline assessment

The baseline questionnaire for patients includes questions on their experiences, concerns, expectations and preferences around dying and end-of-life care. Questions also address health-related quality of life, symptoms, decision-making, social support and attitudes towards euthanasia. Finally, questions are asked about health economic aspects, such as patients’ employment status, use of healthcare and informal care needs. Relatives will also complete a questionnaire about their experiences, concerns, expectations and preferences around the last phase of life of the patient, their own health-related quality of life, their employment status and their provision of informal care. Attending physicians fill in a questionnaire about patients’ diagnosis, comorbidities, life expectancy and their perspective on patients’ current treatment aims. Where possible, validated measures that are commonly used to evaluate important aspects in end-of-life care are used to collect the data (table 2).

#### Follow-up 1

Four weeks after the baseline assessment, patients and relatives are asked to complete a follow-up questionnaire to assess changes as compared with baseline.

#### Follow-up 2

In case a participating patient dies, participating relatives are after 8–10 weeks asked to fill in a post-bereavement questionnaire, to assess their experience of the last days of life of the deceased patient, their appreciation of the quality of end-of-life care and family support, and their bereavement process. The physician or another healthcare staff member who attended the patient in the dying phase is also asked to complete a questionnaire to evaluate care in the dying phase. More specifically, questions will be asked on the place of death, symptoms and if they were treated, whether the patient and the family were informed that the patient was in the final stage of life, how long before death the patient lost the ability to express his/her will, and whether anyone was present at the time of death.

Medical file. Healthcare use in the patient’s last week of life is assessed using a checklist. Items to be assessed include place of care, medical complications, medication use, major medical and surgical interventions and care, goals of care statements, resuscitation policy and non-treatment decisions.Qualitative interviews. More in-depth insight will be obtained in complementary personal interviews with patients, relatives and healthcare professionals. The same eligibility criteria apply as in the cohort study. The sample of interviewees will be controlled for age and gender per country, to allow a comparative analysis. The interviews will be semistructured using a topic guide that is based on Giger-Davidhizar-Haff’s model for cultural assessment in end-of-life care,^25^ the ABCD model for effectively addressing and integrating cultural needs and issues in clinical care,^26^ and perception of disease questions.^27^

During the interviews with patients, questions will be asked about their understanding of the illness, relationship with family, concerns, difficulties to discuss end-of-life topics and decision-making. Comparable questions about these topics will be asked to relatives. Healthcare professionals will be asked questions about the care they aim to provide, collaboration with other professionals, communication with patients, decision-making, and values and beliefs when working with dying patients.

### Translation of questionnaires

Where possible, published and validated versions of existing instruments in the languages of the participating countries will be used. Where necessary, instruments will be translated. An instrument that has been translated correctly is conceptually equivalent to the source instrument^28–30^ and thereby enables collection and pooling data from various linguistic and cultural regions. Translations will be performed according to the standard proposed by the EORTC Quality of Life Group.^31^ The translation process will thus include two forward translations from English to the target language, development of a provisional consensus version, two backward translations and a careful comparison with the original. This will be repeated iteratively until a satisfactory result is obtained. The original developers of the instruments will provide feedback during this process and approve the final translations. Self-developed questions will be developed in English and translated following the same standards. The final translations will also be tested as part of the study questionnaire pilot testing in each country.

### Data management

This study will be conducted in accordance with the General Data Protection Regulation and national research ethics and privacy guidelines.^32^ One common data management system will be used to safely process and store data of all participating patients, relatives and physicians across clinical sites and countries. In some countries, participants can choose to directly enter data into this system; in that case, they consent to use of their email address for communication purposes. In all other cases, data are entered anonymously by selected local research assistants, and a study number will be generated to link data of participants with a local communication database.

### Sample size

The primary outcomes are measured at baseline and 4 weeks post-inclusion. It is expected that 30% of all patients who complete the baseline assessment will be lost to follow-up, due to death, significant deterioration of health or other causes. In that case, 70% of patients who complete the baseline measurement will be able to complete the assessment after 4 weeks at follow-up 1. Further, it is expected that 80% of all patients who complete the baseline assessment can be followed until death, whereas the remaining 20% are expected to either survive until the end of the data collection period or become lost to follow-up. Regarding the relatives, it is expected that in case patients who complete the baseline assessment die during follow-up, half of the bereaved relatives (ie, 40% of all baseline patients), will be willing to complete a post-bereavement questionnaire (follow-up 2). The total cohort would thus include 2200 patients (n=200 per country) at baseline, 1540 patients (n=140 per country) at follow-up assessment 1 and 880 bereaved relatives (n=80 per country). The number of 200 patients per country enables us to estimate proportions with 95% Confidence Intervals (CIs) of approximately ±7%. The number of recruiting sites will vary from two to six per country.

No sample size estimation has been performed for the qualitative interviews since the aim is to explore and better understand the variety in experiences of patients, relatives and physicians, rather than having a representative sample per country.

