### Analysis plan

#### Primary outcomes

The primary outcomes are experiences, concerns, expectations and preferences around dying and end-of-life care of patients in the last phase of life and their relatives, at baseline and after 4 weeks follow-up, and will be described in frequencies and narrative descriptions. The proportion of patients who have certain concerns, expectations and preferences will be described. Subgroup analyses will be performed to assess cross-gender, cross-age and cross-cultural variety on experiences, concerns, expectations and preferences. Narrative descriptions will be translated into English and categorised into themes that will be identified within the data.

Descriptive statistics will be used to summarise baseline characteristics of the study participants (age, gender, education, diagnosis, comorbidities, religion, socioeconomic status, marital status, place of residence, quality of life, symptom load) by country and site. Statistics on mean/median scores and variance will be presented where applicable. Associations with country and patient characteristics will be analysed in a multilevel modelling approach, taking account of clustering effects at country level. Both univariable and multivariable analyses will be performed. All statistical tests will be two-sided and considered significant if p<0.05. Repeated measures analyses of variance will be conducted to assess the development of outcomes between baseline and 4 weeks follow-up. Multivariate Imputation by Chained Equations (MICE) will be used to handle missing data,^33^ as we expect that patients may not be able or want to fill in all questions in the questionnaire. MICE is known to be a flexible principled method of addressing missing data and can handle variables of varying types (eg, continuous or binary). Quantitative analyses will be performed with SPSS V.25.0 statistical software.

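### The ±7% precision per country applies to 200 baseline patients treated as a simple random sample; at 4 weeks the plan's own numbers give ±8.3, and neither the figure nor the stated models allow for site clustering

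*Protocol article*

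**What the plan says.** The Sample size section gives one precision figure. It states that 200 patients per country "enables us to estimate proportions with 95% Confidence Intervals (CIs) of approximately ±7" per cent. The same section sets out the expected numbers: "The total cohort would thus include 2200 patients (n=200 per country) at baseline", then "1540 patients (n=140 per country) at follow-up assessment 1 and 880 bereaved relatives (n=80 per country"). The fall to 140 follows from the expectation that "30% of all patients who complete the baseline assessment will be lost to follow-up".

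Under Analysis plan, Primary outcomes, the primary outcomes are those "of patients in the last phase of life and their relatives, at baseline and after 4 weeks follow-up". The 4-week assessment is therefore a primary time point. The 80 bereaved relatives answer the post-bereavement questionnaire at follow-up 2, which is a different assessment. The number of relatives expected at baseline and at 4 weeks is not stated.

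On sites, the Sample size section says: "The number of recruiting sites will vary from two to six per country". Study design and setting lists 20 hospitals, 7 palliative care institutes and 8 nursing-home-type settings, 35 in all. The Primary outcomes and Secondary outcomes paragraphs both specify multilevel models whose only named clustering level is country. No site level, ICC or design effect appears. The Introduction hypothesises that concerns, expectations and preferences differ by care setting, among other factors.

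**The concern.** The ±7% figure is the only quantitative support offered for 200 patients per country. It describes the most favourable of the samples the section lists: the largest one, with every patient treated as independent. A reader could carry it over to the 4-week results, where the expected sample is 30% smaller, or to comparisons between countries, which are the subject of the second aim and always have wider intervals than a single proportion.

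With two to six sites, a country's 200 patients come in blocks of about 33 to 100. If patients in a nursing home resemble each other more than they resemble patients on an oncology ward, as the Introduction expects for care setting, the effective sample is smaller than 200. A model that names country as its only level leaves that correlation out. Standard errors for country contrasts would then be too small, and differences between sites could be read as differences between cultures.

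**Working it through.** **Inputs.** From the Sample size section: 200 patients per country at baseline, 30% lost by 4 weeks, 80% followed to death, half of the bereaved relatives responding, two to six sites per country, 95% confidence. The section states no proportion, so p = 0.5 (the worst case) is taken. The ICCs are assumptions.

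**Expected numbers.** 200 × 0.70 = 140 and 200 × 0.80 × 0.50 = 80. Both agree with the plan.

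**Half-width under simple random sampling:** 1.96 × √(p(1−p)/n).

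- n = 200: 1.96 × √(0.25/200) = 6.93 points. The plan's figure reproduces.
- n = 140 (4 weeks): 1.96 × √(0.25/140) = 8.28 points.
- n = 80 (bereaved relatives, follow-up 2): 1.96 × √(0.25/80) = 10.96 points.

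The widening relative to baseline does not depend on p: √(200/140) = 1.20 and √(200/80) = 1.58.

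**Difference between two countries**, independent samples, p = 0.5 in each: 1.96 × √(0.50/n).

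- n = 200: ±9.8 points.
- n = 140: ±11.7 points.

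**Site clustering.** With k equal-sized sites, m = n/k and the design effect is 1 + (m − 1) × ICC. The half-width is multiplied by its square root. Worked case: n = 200, two sites, ICC 0.01 gives 1 + 99 × 0.01 = 1.99, so 200/1.99 ≈ 100 effective patients and 6.93 × √1.99 = 9.8 points.

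Half-widths in points, six sites to two sites:

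| Assumed site ICC | n = 200 | n = 140 | n = 80 |
|---|---|---|---|
| 0 | 6.9 | 8.3 | 11.0 |
| 0.01 | 8.0 to 9.8 | 9.2 to 10.8 | 11.6 to 12.9 |
| 0.02 | 8.9 to 12.0 | 10.0 to 12.8 | 12.2 to 14.6 |
| 0.05 | 11.2 to 16.9 | 12.0 to 17.5 | 13.9 to 18.8 |

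Only the first row rests on the plan's own numbers. The 35 settings over 11 countries average about 3.2 per country (2200/35 ≈ 63 patients each), so two sites is the extreme and not the typical case. At three sites the n = 200 figures are 8.9, 10.5 and 14.3 for the three ICCs. The multiplier 1.96 treats the ICC as known; it would be too small if the site variance had to be estimated from one country's few sites.

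**The case against.** The ±7% sentence names its own scope, 200 patients per country, and is right for that scope. It makes no claim about 4 weeks, relatives or between-country differences. A reader might infer an arithmetic error; there is none.

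A reader might also infer that the plan's own numbers reach about ±15. They stop at ±11.0. Getting to 14.6 takes an assumed ICC of 0.02 together with the smallest sample and the fewest sites. Nor are the 80 bereaved relatives the sample for the relatives' primary outcomes, since those are measured at baseline and 4 weeks and their numbers are not given. Finally, published intervals will be computed from the observed data, so a planning figure cannot by itself make them too narrow. All of this stands.

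Two further arguments stand in part. First, for proportions far from 50% the 4-week half-width is still ±7 or less (p below about 0.23 or above about 0.77). But the baseline half-width shrinks equally, so the loss of precision between the two time points remains. Second, sites chosen deliberately for diversity can be treated as fixed strata, in which case no design effect is required. The results then describe those sites, whereas the plan attributes its proportions and contrasts to countries and cultures. For that target, variation between sites belongs in the error.

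The full protocol or an analysis plan may say more about site. The article does, however, fix both the precision figure and the clustering level, so these can be judged as stated.

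**Conclusion.** The point holds as one of incomplete and optimistic precision. At the 4-week primary time point the plan's own attrition takes ±6.9 to ±8.3, a factor of 1.20, and no assumption is needed beyond the p = 0.5 that already underlies ±7%. For bereaved relatives at follow-up 2 the figure is ±11.0.

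Site clustering is omitted both from the precision figure and from the stated models. How much that matters depends on an ICC that the article does not give. Over assumed values from 0.01 to 0.05, the baseline half-width runs from about ±8.0 (ICC 0.01, six sites) to ±16.9 (ICC 0.05, two sites), with equal-sized sites. If there is no correlation within sites, or if inference is confined to the participating sites, that part falls away and the 4-week part remains.

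The effect on published results would come through the country-only models and not through the planning sentence. This is a minor to moderate correction for a largely descriptive cohort.

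**What to change.** In the Sample size section:

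- Label ±7% as applying to *baseline patients, ignoring site clustering*.
- Add ±8.3 for patients at 4 weeks and ±11.0 for bereaved relatives at follow-up 2, with a range over stated, assumed site ICCs such as 0.01 to 0.05.
- Add the half-width of a difference between two countries: ±9.8 at baseline and ±11.7 at 4 weeks, before clustering.

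In the Primary outcomes and Secondary outcomes paragraphs, add site nested within country to the multilevel models, fitted across all of the roughly 35 sites. With 11 countries this leaves about 35 − 11 = 24 degrees of freedom for variation between sites within countries, on the assumption that this variation is similar across countries. Do not rely instead on site-robust standard errors computed country by country: with two to six clusters they are unreliable and tend to be too small.

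The cost is a less favourable stated precision and somewhat wider intervals. No extra patients or data are needed, because sites are already recorded for the planned summaries by country and site.
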